### Selection of Participants and Sample Size Calculation

The study participants will be selected from the city of Bauru, São Paulo, Brazil, which has a population of 371,690 inhabitants and a Human Development Index of 0.801. Participants aged 6-10 years will be selected from an epidemiological survey in municipal schools. These schools are located in an urban area, in different zones (north, south, east, and west), and will be selected by a draw according to each zone. In the selected schools, all children aged 6-10 years will be evaluated. Children with potential for inclusion in the research will be referred for a clinical examination at the pediatric dentistry clinic of Bauru School of Dentistry, University of São Paulo, and those that have at least one first permanent molar affected by MIH with hypersensitivity complaint and without loss of structure will be invited to participate. The sensitivity complaint will be confirmed by applying a 1-second air jet at a distance of 1 centimeter from the occlusal surface of the tooth; a score of 2 or 3 on the Schiff Cold Air Sensitivity Scale (SCASS) will be considered as a positive result. Patients with orthodontic appliances, syndromes that involve enamel malformation, or behavioral problems during the clinical examination will be excluded. 

The sample size was calculated considering analysis of variance, performed in SigmaPlot (version 12.3; SPSS Inc), and it was considered a minimally detectable difference of 1 on the SCASS scores between groups. A standard deviation of 0.9 was used based on a previous study [28], α error was 5%, β error was 20%, and a dropout rate of 18% was used, which resulted in a total of 60 children (20 per group). The first 60 children who meet the inclusion criteria will be selected to be part of the study, while others who also present with sensitivity but cannot be included will receive the necessary treatment.

Recruitment will take place from October 2019 to December 2021. After allocation and treatment for 4 weeks, the patients will be followed up for 6 months.

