### Primary Outcome: Treatment Effectiveness

A single trained, calibrated, and blinded examiner (not involved in the treatment application) will assess the sensitivity effectiveness of treatment in all groups at different moments: (1) before the application of each material, (2) immediately after application or simulation, (3) one month after the last application/simulation, (4) two months after the last application/simulation, (5) four months after the last application/simulation, and (6) six months after the last application/simulation. For all evaluations, the WBFPS, SCASS, and FLACC scale will be used as previously described.

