### Data Analysis

Statistical analysis will be performed with SigmaPlot (version 12.3; SPSS Inc). For the WBFPS, SCASS, and FLACC scale, the three groups and evaluation time will be compared by 2-way repeated measures analysis of variance followed by a Tukey test, based on the recommendation of Cohen [31], to allow for interaction analysis between study factors and to avoid an inflated α error. A Spearman correlation test will be performed to determine if there is a significant correlation among the WBFPS, SCASS, and FLACC scale. The significance level will be set at 5%. Poisson regression will be used to assess the influence of IPV, GI, and discomfort on the outcome. The satisfaction of parents/guardians and participants will be analyzed descriptively.

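### The repeated measures ANOVA in its standard form needs a complete series from each child, so dropouts, protocol exclusions and missed visits would all draw on an 18% allowance with no slack; a mixed model would use every reading

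*Protocol article*

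**What the plan says.** The Data Analysis section of the protocol article states that, for the Wong-Baker, Schiff (SCASS) and FLACC scales, groups and evaluation times will be "compared by 2-way repeated measures analysis of variance followed by a Tukey test", in SigmaPlot 12.3. It does not say how a missing reading is treated.

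The Primary Outcome section calls for readings before each application, immediately after application or simulation, and at four follow-up times, beginning with "3) one month after the last application/simulation, (4) two months after the last application/simulation" and continuing to months four and six. With four weekly sessions (Treatment Protocol), that makes eight visits and up to 4 × 2 + 4 = 12 readings per child.

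Follow-up Examinations excludes a child once breakdown affects dentin or a cavitated carious lesion appears. The Discussion repeats this and describes MIH as a condition that can worsen. Results reports that one of the first six treated children was excluded at month 1, after the study tooth was restored elsewhere.

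The sample size section gives "it was considered a minimally detectable difference of 1 on the SCASS scores between groups", an SD of 0.9, and "α error was 5%, β error was 20%, and a dropout rate of 18% was used". The planned enrolment is 60, with 20 in each arm.

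**The concern.** A classical two-way repeated measures ANOVA with time as the within-child factor needs a value in each time cell. If it is applied in that form, a child with one empty cell contributes nothing, however many valid readings were taken.

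Two things are at stake.

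- **Bias.** The protocol itself removes children whose tooth has deteriorated. That loss is tied to the course of the condition and may be related to response to treatment. Analysing only children with complete series would leave out those who worsened, together with their valid early readings. This risk does not depend on any assumed rate of missed visits.
- **Precision.** The 18% allowance is described as a dropout rate. Under a complete-series analysis it must cover dropouts, protocol exclusions and every child who stays but misses one reading.

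**Working it through.** **Inputs from the sample size section.** Three arms, difference 1 SCASS point, SD 0.9, alpha 0.05, power 80%, dropout 18%, 20 children per arm. No repeated-measures inputs are given, so the basis is a one-way ANOVA at a single time point.

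**Assumption on the means.** Two arms lie 1 point apart with the third midway (0, 0.5, 1). The sum of squared deviations is 0.25 + 0 + 0.25 = 0.5.

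**Formula.** Noncentrality λ = n × 0.5 / 0.9² = n / 1.62. Power is the probability that a noncentral F with 2 and 3(n − 1) degrees of freedom exceeds the central 5% critical value.

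**Step 1: reproduce the plan's figure.**

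- n = 16: λ = 9.88, power 78.2%
- n = 17: λ = 10.49, power 80.9%

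So 17 complete children per arm (51 in total) are needed. Multiplying by 1.18 gives 20.06 per arm and 60.18 in total, which rounds to the stated 20 and 60. Dividing by 0.82 would give 20.7, that is 21 per arm and 63 in total.

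**Step 2: what the allowance leaves.** 20 × 0.82 = 16.4 per arm (49.2 in total), power 79.3%. The planned dropout alone uses the whole allowance. With no planned dropout, 20 − 17 = 3 children per arm (15%) can be incomplete before the number falls below 17.

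**Step 3: add missed visits.** The protocol gives no missed-visit rate. I assume independent misses at rate m per visit over the seven visits after the first, with only complete series analysed. The complete fraction is (1 − m)⁷.

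| m | (1 − m)⁷ | Complete, no other dropout (of 60) | Power | Complete after 18% dropout (of 49.2) | Power |
|---|---|---|---|---|---|
| 1% | 0.932 | 55.9 | 85% | 45.9 | 76% |
| 2% | 0.868 | 52.1 | 82% | 42.7 | 73% |
| 3% | 0.808 | 48.5 | 79% | 39.8 | 69% |
| 5% | 0.698 | 41.9 | 72% | 34.4 | 62% |

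**Step 4: break-even.** With no other loss, the number falls to 17 per arm when (1 − m)⁷ = 17/20 = 0.85, so m = 1 − 0.85^(1/7) = 2.3% per visit. Once the 18% has been spent, any further miss lowers power from 79%.

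These powers are for a comparison at one time point, which is how the trial was sized. They are not the power of the group-by-time test.

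**The case against.** **The plan does not state whole-child deletion.** A reader might infer that it does. The Data Analysis section names the test and the software and is silent on empty cells. Deletion follows from the standard form of the method, and the software's handling cannot be checked from the document. This stands, and the point is worded accordingly.

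**Missing-data rules are commonly left to a full protocol or SAP.** This is true, and silence on those rules is not the point here. The article does fix the method of analysis, and that choice can be assessed.

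**The fall below 80% is not inevitable.** A reader might infer that any missed visit takes the trial below its powered number. The table does not support that: with no other dropout, power is still about 85% and 82% at 1% and 2% missed. The one exclusion among six children is too few to set a rate, and it was not a missed visit.

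**The power figures are not for the planned test.** This also stands. As an illustration, suppose the 1-point pattern holds at all four follow-up readings and their average is tested. The SD becomes 0.9 × √((1 + 3ρ)/4), where ρ is the within-child correlation, which the protocol does not give. At the worst row of the table (34 children), power would be about 83% at ρ = 0.5 and 65% at ρ = 0.9.

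**Attendance driven by product performance is speculation.** A reader might infer that children stay away according to how well the product works. The document offers no support for this, and children, parents and examiners are to be blinded. The bias argument rests on the documented exclusions for dentin breakdown and cavitated caries.

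**Conclusion.** The concern holds in conditional form. The named method, in its standard form, would discard every reading from any child with an incomplete series. The protocol itself creates such children by excluding those whose tooth deteriorates, so the risk is bias as well as lost precision.

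The size of the power loss rests on assumed rates. On the protocol's own single-time-point basis the allowance has no slack: 17 per arm are needed and 16.4 remain after the planned dropout. Depending on whether the full 18% also occurs, assumed misses of 1–5% per visit give about 76–62% or about 85–72%. The document does not show that the repeated measures test will fall below 80%. The size of any bias cannot be computed from it.

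This should be changed, because a better-suited method is available at little cost. It does not invalidate the design.

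**What to change.** In Data Analysis, replace the two-way repeated measures ANOVA as the primary analysis with a likelihood-based linear mixed model. Group, time and group-by-time are fixed effects, and repeated readings are modelled within child. State that every available reading from every randomised child enters, including readings taken before dropout or protocol exclusion. This keeps the interaction assessment that the authors want, and Tukey-adjusted comparisons can still be made from the fitted means. Keep the complete-series ANOVA as a sensitivity analysis.

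No new data or visits are needed. The costs are revised wording, possibly software other than the package named, and a missing-at-random assumption: the missing readings must be explained by those observed. That assumption may not hold fully for children excluded after deterioration, but it is weaker than what the complete-series analysis needs.

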**Methods:**

A total of 60 children aged 6-10 years presenting with at least one first permanent molar with sensitivity and no loss of enamel will be randomly assigned to three groups: the control group (sodium fluoride varnish; Duraphat, Colgate); experimental group I (4% titanium tetrafluoride varnish); and experimental group II (a coating resin containing surface prereacted glass-ionomer filler; PRG Barrier Coat, Shofu). The sodium fluoride varnish and 4% titanium tetrafluoride varnish will be applied once per week for 4 consecutive weeks and the PRG Barrier Coat resin will be applied in the first session and the application will be simulated the following 3 weeks to guarantee the blinding of the study. The primary outcome will be sensitivity level measured at different moments (before each material application, immediately after application or simulation, and 1, 2, 4, and 6 months after the last application/simulation) by one examiner using the Wong-Baker FACES Pain Rating Scale, the Schiff Cold Air Sensitivity Scale, and the FLACC (Face, Legs, Activity, Cry, Consolability) scale. As secondary outcomes, parental satisfaction and child self-reported discomfort after the treatment will be measured with a questionnaire prepared by the researcher. The data will undergo statistical analysis and the significance level will be set at 5%.

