**Conclusions:**

If found effective in reducing the patient’s sensitivity long term, these agents can be considered as a treatment choice, and the findings will contribute to the development of a treatment protocol for teeth with sensitivity due to MIH.

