### Treatment Protocol

All children will receive instructions on noncariogenic diet and oral hygiene. Furthermore, the participants will receive an oral hygiene kit with toothbrush and fluoride toothpaste (both Colgate-Palmolive Company). Immediately before treatment, a supervised toothbrushing will be performed with a fluoride-free toothpaste to standardize the treatment phase and to follow the instructions of the S-PRG resin manufacturer. The study risks for participants are minimal and related to the sensitivity due to MIH.

In the control and experimental I groups, the fluoride varnishes will be applied once per week for 4 consecutive weeks. For the experimental II group, the product will be applied the first week and the application will be simulated the following 3 weeks for patient blinding.

All children in the control and experimental I groups will be treated according to the same protocol:

Supervised toothbrushing with fluoride-free toothpaste.Cotton roll isolation of the area.Drying of the tooth using sterile gauze.Varnish application with microbrush according to the manufacturer’s instructions.Instruction of the patient not to eat or drink for 30 minutes and not to brush for at least four hours after application.Reapplication once per week for 3 weeks, following the described protocol.Follow-up.

For the experimental II group, the treatment protocol according to the manufacturer is as follows:

Supervised toothbrushing with fluoride-free toothpaste.Cotton roll isolation of the area.Drying of the tooth using sterile gauze.Material handling within 2 minutes after mixing.Application of a thin layer with the device provided by the manufacturer, then a 3-second wait.Light curing for 10 seconds.Instruct the patient to avoid colored drinks and food for 3 days.Application simulation the following 3 weeks (repeat steps 1-3).Follow-up.

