### Sensitivity Assessment

Sensitivity will be assessed before and after treatment (for all groups) using three instruments: the Wong-Baker FACES Pain Rating Scale (WBFPS), SCASS, and FLACC (Face, Legs, Activity, Cry, Consolability) scale, as described below.

First, the researcher will ask whether the child feels any discomfort in his/her teeth. The researcher will also carefully explain that their WBFPS face choice should be related to the toothache and not the child’s mood at that moment. The child will then be shown the WBFPS, and the child will be guided to choose the most representative face.

Second, sensitivity will be clinically assessed by applying a 1-second air jet 1 centimeter from the buccal and occlusal surfaces of the tooth. The adjacent teeth will be protected with cotton rolls and the patient’s response to the stimulus will be evaluated according to the SCASS. The child's reaction will be recorded according to the codes described in Multimedia Appendix 1.

Third, the examiner will also record the patient's reaction using the FLACC scale (Multimedia Appendix 2). This scale has 5 categories and the responses to each one will be scored from 0 to 2. In each category, the numbers obtained will be summed to obtain the total pain score (0-10). Finally, the child will be asked about discomfort in their teeth again following the use of the air jet and the WBFPS will be applied again.

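### Three scales are jointly primary, each tested at 5%; the stated protection against an inflated α works within one scale and does not reach across the three

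*Protocol article*

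**What the plan says.** - **Primary outcome.** The Abstract (Methods) states: "The primary outcome will be sensitivity level measured at different moments". The section Primary Outcome: Treatment Effectiveness lists six kinds of moment, beginning "1) before the application of each material, (2) immediately after application or simulation" and continuing with follow-ups at 1, 2, 4 and 6 months. It adds: "For all evaluations, the WBFPS, SCASS, and FLACC scale will be used as previously described". Neither place names a lead scale or a lead moment.
- **Analysis.** Data Analysis applies a two-way (group, time) repeated measures ANOVA, then Tukey, to WBFPS, SCASS and FLACC. The reason given is "to allow for interaction analysis between study factors and to avoid an inflated α error". The level is 5%, with no split or ordering across scales. The set of means that Tukey covers is not stated.
- **Sample size.** Only one scale enters: "it was considered a minimally detectable difference of 1 on the SCASS scores between groups", with SD 0.9, α 5%, power 80% and dropout 18%, giving 60 children.
- **Surface.** Selection of Participants confirms sensitivity with an air jet to the occlusal surface and requires SCASS 2 or 3. Sensitivity Assessment reads the outcome by "applying a 1-second air jet 1 centimeter from the buccal and occlusal surfaces of the tooth". It does not say how two surfaces yield one score.
- **WBFPS.** Sensitivity Assessment collects it before and again after the air jet. Data Analysis names it once.

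**The concern.** The protocol itself fixes the primary outcome, the test, the level and a statement about α, so this is not simply a detail left to a later analysis plan. Followed as written, the trial yields three primary analyses at 5% each. A positive result on any one of them could be reported as the primary finding, and there is no rule for the case where the scales disagree. Tukey protects comparisons among means inside one ANOVA. It knows nothing of the other two ANOVAs, so the stated aim of avoiding an inflated α is not met for the primary outcome as a whole.

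The surface difference adds a second ambiguity to the one scale that was sized: the score that qualifies a child need not be the score that is later analysed.

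**Working it through.** **1. The plan's own sample size.** Inputs from Selection of Participants and Sample Size Calculation: difference 1, SD 0.9, three groups, α 0.05, power 0.80, dropout 18%.

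Noncentral F with λ = n·δ²/(2·SD²). At n = 17, λ = 17/(2 × 0.81) = 10.49 and power is 0.809. At n = 16 power is 0.782. So 17 per group are needed.

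Dropout as 17 × 1.18 = 20.06 gives 20 per group and 60 in total, the stated figure. Dividing instead, 17/0.82 = 20.7, gives 21 per group and 63 in total. The stated 60 is thus reproduced by the first route, for one SCASS comparison at an undivided 5%.

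**2. Ceiling across three scales.** One 5% test per scale, if independent: 1 − 0.95³ = 14.3%.

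**3. Simulation of the planned model under no treatment effect.** Settings: 16 children per group (20 × 0.82 = 16.4), 12 readings, three scales, normal data with equal correlations, 8,000 runs. The 12 readings are inferred: the treatment runs over weekly visits ("the fluoride varnishes will be applied once per week for 4 consecutive weeks"), so up to 4 before, 4 after and 4 follow-ups. The document gives no count, and it would be 6 if before and after are each read once. Correlations are assumptions; between readings 0.5 was used, with 0.8 as a check.

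| Between-scale correlation | Group-by-time test, one scale | Group-by-time test, any of three | Group or interaction test, any of three | Tukey at each moment, any of three |
|---|---|---|---|---|
| 0 | 5.0% | 14.2% | 26.2% | 70.3% |
| 0.3 | 4.8% | 13.7% | 26.1% | 69.0% |
| 0.5 | 5.3% | 13.4% | 24.9% | 66.6% |
| 0.7 | 4.7% | 11.6% | 21.2% | 60.0% |
| 0.9 | 4.7% | 8.7% | 16.7% | 50.4% |

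With correlation 0.8 between readings and 0.5 between scales, the four results are 5.2%, 13.2%, 25.0% and 43.7%. Simulation error near 14% is about √(0.14 × 0.86/8000) = 0.4 percentage points.

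The second column shows that the omnibus test for a single scale keeps its 5% however many readings enter. The excess in the third column comes from having three scales. The last column applies only if Tukey compares the three groups separately at each reading; the error is then about 33% for one scale (20% at between-reading correlation 0.8). If Tukey covers all group-by-time means of a scale, that scale is controlled.

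**4. Cost of keeping three primaries.** At α = 0.05/3 = 0.0167 each, 22 evaluable per group are needed; 22/0.82 = 26.8, so 27 per group and 81 in total. At 16 evaluable per group, power would be 62% instead of 78%.

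**The case against.** The α phrase explains why ANOVA with Tukey is preferred to many pairwise tests, and within one scale that is sound. SCASS already leads in practice: it drives eligibility, stratification and sample size, and the Discussion calls the face scale subjective. A full analysis plan may fix the Tukey family. All this is fair. It limits the point to control across scales and does not remove it, because both statements of the primary outcome still give the three scales equal standing.

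Stronger readings are tempting but are not supported:

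- **Every reading is tested at 5%.** A reader might count 12 readings on three scales as 36 tests, which would give 1 − 0.95³⁶ = 84%. Data Analysis puts all readings of a scale into one model, so this is not the plan.
- **The α statement is false.** It makes no explicit claim about control across scales, and it is reasonable within one.
- **WBFPS counts as two endpoints.** It is collected twice, but only one analysis of it is named.
- **Stratification uses a different score from the analysed baseline.** Random Allocation asks for equal SCASS scores within a block and names no surface, so a mismatch there is not shown.
- **A fall within one arm would count as success.** The Abstract's conclusion that "these agents can be considered as a treatment choice" if effective is conditional wording, not a decision rule. The stated aim and the analysis compare the three groups. Any figure for regression to the mean would need a population mean and retest correlation that the document does not give.

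**Conclusion.** The point holds in this form: three scales are jointly primary at 5% each, with no lead scale, no lead moment and no control across scales. The chance of at least one false group-by-time result is about 9% to 14%, with a ceiling of 14.3%. It is about 17% to 26% if group and interaction tests both count, and about 44% to 70% if Tukey is run separately at each of 12 readings. The 14.3% ceiling is plain arithmetic; the other figures rest on the assumed correlations, normal data and, for the last range, the inferred 12 readings and an unstated Tukey family. The surface difference between entry and outcome is plain in the text; its effect on the results cannot be sized from the document.

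**What to change.** 1. Name SCASS on the drawn tooth as the single primary scale, with one stated surface rule used for both entry and outcome.
2. Name one primary moment. Six months is an example, as the last planned follow-up; it is a choice among the listed moments, and the investigators should weigh it against exclusions and repeat treatment during follow-up.
3. Make the between-arm comparison of the three groups at that moment the primary test, and base the conclusion on it.
4. Make FLACC, both WBFPS readings and the other moments secondary.
5. Limit the α statement to comparisons within one scale, and state which means the Tukey family covers.

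The planned 60 children are unchanged, since the calculation already rests on SCASS at an undivided 5%. The cost is mainly wording, to be settled before outcome data are analysed. Because Results reports 6 children already treated, the sponsor should check that their records allow the chosen surface rule. The scientific cost is that FLACC and WBFPS findings become supportive only.
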